# 5.0 Recruitment Strategy

The study population will consist of six groups of apparently healthy 50-64y old men and women (n=24 per group) with low plasma (or serum) selenium. The volunteers will be recruited until 144have completed the study. Experience has shown that the drop out rate for these types of study is 25%. If a greater drop out rate occurs recruitment will be reviewed.

Advertisements (annex 3) will be placed around the Norwich Research Park (University of East Anglia (UEA), John Innes Centre (JIC), and IFR, in the HNU news letter (which is sent to all volunteers on the HNU volunteer database) in the local press and other suitable locations for example, supermarkets, social clubs, church news letters and golf clubs, gymnasiums and leisure facilities within the local area (40 mile radius). As in the past we will also obtain radio coverage and place advertisements (Annex 17 and 18) in the press to raise local awareness of the project if need be. The posters advertising this study will also be supplied with business cards or other suitable appendages to the poster in order to facilitate volunteer recruitment.

Apparently healthy volunteers from the HNU volunteer database, who meet the basic inclusion criteria, will be sent a letter of invitation (annex 2) to participate in the study. This will be supported by the volunteer information sheet (annex 4). Included will be a response slip and pre-paid envelope for returning the slip if they are interested and wish for further information. The HNU database has approximately 383 people between the ages of 50 and 64 years who are willing to participate in dietary intervention studies. It is known that at least 278 of these are non-smokers, and contact will made with these individuals.

Advertisements will also be placed on appropriate noticeboards in the Norfolk & Norwich University Hospital and on the NNUH intranet. Approaches will be made to GP practices via the Primary Care Research Network. In this instance, the GP will send out letters of invitation to individuals who meet the basic inclusion criteria. This will be supported by the volunteer information sheet and a response slip and pre-paid envelope for returning the slip directly to IFR if they are interested and wish for further information.

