## 6.4 Volunteer Randomisation

Ideally the study would be completely randomised, but this would compromise our ability to complete recruitment in the time allowed i.e. only accepting volunteers onto the study that like onions so that they could be randomised into any one of six groups (years 2 and 3 only as year one is the supplement study only). It would also beunethical to accept volunteers who had a dislike or intolerance to onions onto the onion part of the study.  Volunteers will as far as possible be randomly allocated to one of four groups in year one (0µg/day (placebo), 50µg/day, 100µg/day and 200µg/day of Se-yeast) and one of six groups in years 2 and 3 (the selenium supplements above as well as selenium-enriched and un-enriched onion groups).  There is no evidence to suggest that volunteers who do not or cannot eat onions will display any differences in immune function response or selenium status to those volunteers that do, and thus there will be no consequences of the study not being fully randomised.  However, as this is a new area of research, the preferences of all subjects recruited in the first year of the study will be monitored, and the possibility of differences by onion “preferences” investigated. Volunteers will be stratified by sex. The volunteer information document (annex 4) will clearly state that volunteers recruited in 2005 will be assigned to the supplement study only.

|  | Volunteers to be recruited | | |
| --- | --- | --- | --- |
|  | Selenium-enriched onions | Un-enriched onions | Selenium-Supplementation |
| Year 1 (2005-2006) | n=0 | n=0 | n=32 |
| Year 2 (2006-2007) | n=12 | n=12 | n=32 |
| Year 3 (2007-2008) | n=12 | n=12 | n=32 |

Table 1: Study groups outlined

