# 7.0 Statistical Analysis

Power calculations were done so that, out of the six study groups, a difference of 1 standard deviation in response variable between the minimum and maximum responding groups would be reliably detected. For example, for plasma selenium, previous studies (Shortt et al, 1997) suggest that the population standard deviation is 11.7, and so our sample sizes are designed to give an 80% chance of detecting a range of plasma selenium between the six groups of 11.7. For antibody secreting cells/500,000 lymphocytes and specific serum antibody (both at day 7 post-vaccination) the corresponding standard deviations are 76 and 19 respectively (Cox et al, 1999).

The power calculations also assumed that any effect of selenium supplementation would be proportional to the amount of supplementation, with enriched onions being equivalent to a supplementation of 50µg/day selenium and the un-enriched onions equivalent to no supplementation.

The power calculations were also based on the assumption that the data would be analysed using a one-way ANOVA model, the grouping having six levels (control, 50µg/day selenium, 100µg/day selenium, 200µg/day selenium, enriched onions, non-enriched onions). In order to be able to detect a range of 1 standard deviation between the groups with a power of 80%, a sample size of 144 (or 24 in each group) is sufficient. This allows for a drop-out rate of 25%, or in other words, finishing with 18 subjects in each group.

In the unlikely event of there being a year effect, and thus the two onion groups (but not the control and supplementation groups) being potentially compromised,24 subjects in each of the remaining 4 groups gives a power of 80% of detecting a range of 1 standard deviation in the response variable. This is based on using a two-way ANOVA model to analyse the data, with a three level year effect and a four level group effect (control, 50µg/d Se, 100µg/d Se, 200µg/d Se). It is important to stress however that we are aiming to recruit the full complement of 24 volunteers without the drop out rate of 25% as we feel there is a greater chance of compliance with the supplementation intervention.

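### The recruitment target is given both as 144 completers and as 144 recruits (108 completers), and the drop-out allowance behind the power figures changes between arms

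*Protocol*

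**What the plan says.** All references are to the protocol.

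- **Section 5.0 (Recruitment Strategy)** sets the end of recruitment by completers: "The volunteers will be recruited until 144have completed the study". It puts the usual drop-out for such studies at 25% and says recruitment will be reviewed if the loss is greater.
- **Section 6.4, Table 1**, is headed "Volunteers to be recruited". It lists 24 for enriched onions, 24 for un-enriched onions and 96 for supplementation over the three years.
- **Section 7.0 (Statistical Analysis), six groups.** The aim is that "a difference of 1 standard deviation in response variable between the minimum and maximum responding groups would be reliably detected". The pattern of means is fixed by the assumption that "any effect of selenium supplementation would be proportional to the amount of supplementation", with enriched onions counted as 50 µg/day and un-enriched onions as none. The conclusion is "with a power of 80%, a sample size of 144 (or 24 in each group) is sufficient", followed at once by "This allows for a drop-out rate of 25%, or in other words, finishing with 18 subjects in each group".
- **Section 7.0, fallback if there is a year effect.** For the placebo and three Se-yeast groups in a two-way ANOVA with year, "24 subjects in each of the remaining 4 groups gives a power of 80% of detecting a range of 1 standard deviation". The same paragraph says the full 24 are expected in these groups without the 25% loss, because better compliance is anticipated with supplements.
- **Section 7.0, onion groups analysed alone.** The figure returns to 18 per group, with the 25% loss tied to the onion intervention.

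No significance level is stated.

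**The concern.** The number 144 cannot be both the count that finishes and the count that starts when a quarter are expected to leave. Staff who follow Section 5.0 would go on recruiting after staff who follow Table 1 had stopped. Other parts of the plan depend on the number. Table 1 sets yearly quotas, Section 6.1 says the weekly number of immune assays is limited, and Section 6.51 sizes the onion crop for 24 subjects in each onion arm.

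The power statements inherit the problem. The six-group 80% is attached to 24 recruited and 18 finishing. The four-group 80% is attached to 24 with no loss. A reader cannot tell which number of analysed volunteers the trial relies on, or at what alpha.

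**Working it through.** **1. Recruits and completers**

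- Table 1: 12 + 12 + 12 + 12 + 32 + 32 + 32 = 144 recruits.
- Section 7.0, 25% loss in every arm: 24 × 0.75 = 18 per group; 6 × 18 = 108 completers.
- Section 7.0, loss in the onion arms only: 4 × 24 + 2 × 18 = 132 completers.
- Section 5.0: 144 completers; 144 / 0.75 = 192 recruits, or 32 per group.
- Gap between Section 5.0 and Section 7.0 (loss in every arm): 192 − 144 = 48 recruits; 144 − 108 = 36 completers.

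**2. Inputs for power**

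- Range of 1 SD and dose-proportional means (Section 7.0). In SD units: placebo 0, 50 µg 0.25, 100 µg 0.5, 200 µg 1, enriched onions 0.25, un-enriched onions 0.
- One-way ANOVA with six levels; the fallback is a two-way ANOVA with four groups and three years (Section 7.0).
- Alpha: not stated. Assumed 0.05, with the effect of other values shown.

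**3. Formula**

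With equal groups of size n, the noncentrality is λ = n × Σ(mean − grand mean)². Power is the probability that a noncentral F with parameter λ exceeds the central F critical value.

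- Six groups: grand mean 2/6 = 0.333; Σ = 1.375 − 6 × 0.1111 = 0.7083.
- Four groups: grand mean 1.75/4 = 0.4375; Σ = 1.3125 − 4 × 0.1914 = 0.5469.

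**4. The plan's six-group 80%**

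At n = 18, λ = 18 × 0.7083 = 12.75.

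- Large-sample noncentral chi-square, 5 df: 79.7%. This reproduces the stated 80% to rounding and shows that the figure belongs to 18 finishing per group.
- Exact F with 5 and 102 df: 77.2% (simulation 77.5%).
- Exact F at n = 19: 79.9%; at n = 20: 82.3%.
- Detectable range at 80% power with n = 18: 1.03 SD. For plasma selenium, where earlier work is said to "suggest that the population standard deviation is 11.7", this is 1.03 × 11.7 ≈ 12.1 instead of 11.7.
- Effect of alpha at n = 18: an alpha of about 0.062 gives exactly 80%, and 0.10 gives 85.9%.

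**5. Six-group power under each reading of the target (exact F, alpha 0.05)**

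| Reading | Recruits | Completers | Power |
|---|---|---|---|
| 25% loss in all arms | 144 | 108 | 77.2% |
| 25% loss in onion arms only | 144 | 132 | 88.0% |
| 144 completers, 25% loss | 192 | 144 | 89.7% |

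For the middle row, the weighted mean is (24 × 1.75 + 18 × 0.25) / 132 = 0.3523, and λ = 32.625 − 132 × 0.1241 ≈ 16.24, with 5 and 126 df.

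**6. Four-group fallback (year additive, alpha 0.05)**

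- n = 24, as the plan states: λ = 24 × 0.5469 = 13.13; error df 90; power 85.8%. The 80% claim holds.
- n = 18, if the 25% of Section 5.0 also applied here: λ = 9.84; error df 66; power 72.6% (75.4% by the large-sample method). About 21 completers per group are needed for 80%.

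**The case against.** The strongest defence is that only the recruitment wording is at fault and the power figures are sound.

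Much of this stands. A reader might infer that the six-group 80% is an arithmetic error. The documents do not support that: the 77.2% rests on an alpha the protocol never gives, the large-sample method returns 79.7%, and the shortfall is one to two completers per group. A reader might also infer that the four-group 80% is wrong. It is not. It is claimed at 24 per group, where exact power is about 86%. It falls to about 73% only if a loss is imposed that Section 7.0 expressly waives for those groups. That expectation may be optimistic beside the general 25% in Section 5.0, but it is a stated planning assumption.

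Two further inferences should not be drawn. One could get lower power by placing the intermediate groups midway between the extremes, but Section 7.0 commits to effects proportional to dose. One could also read Section 5.0 as implying replacement of drop-outs or a completers-only analysis. The protocol says neither, and the analysis set is commonly defined in the SAP, which is not at hand.

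The defence does not remove the conflict over the target. Section 5.0 cannot be reconciled with the 18 finishers per group in Section 7.0, and its promise to review recruitment covers only losses above 25%.

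**Conclusion.** The contradiction in the target follows from the protocol's own text and needs no outside figure: 144 completers (about 192 recruits) in Section 5.0, against 144 recruits in Table 1 and Section 7.0. Within Section 7.0 the drop-out allowance also differs between paragraphs, so 144 recruits may mean 108 or 132 completers.

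Six-group power runs from about 77% to about 90% across the three readings, given dose-proportional means, a 1 SD range and an assumed alpha of 0.05. None of them undermines the design. The six-group shortfall at 108 completers is minor, and the four-group figure is correct on its stated condition. The point should be corrected as an inconsistency and not reported as a failure of power.

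**What to change.** State one target, one drop-out assumption per arm, and alpha, and use them in Sections 5.0, 6.4 and 7.0.

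- **Without enrolling more.** Replace the completer rule in Section 5.0 with 144 randomised (24 per group). State the expected completers: 108 if 25% are lost in every arm, or 132 if only the onion arms lose 25%. Give the matching six-group power by exact F at alpha 0.05 (if that is the level intended): about 77% or about 88%.
- **If 144 completers is the real intention.** Keep the rule, state that it means about 192 recruits at 25% drop-out with about 90% six-group power, and change Table 1 and Section 7.0 to match.
- **In either case.** Label the four-group two-way figure as conditional on 24 completers per group (about 86%). With 24 recruited per group, note that it would be about 73% if the 25% loss in Section 5.0 also applied to those arms.

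The first option costs only protocol wording, and with 25% loss in all arms a slightly less favourable power figure. The second costs 48 more volunteers, with the assays, tablets and onion meals they need.

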In order to allow for the unlikely possibility of a year effect the control group and each of the three selenium supplementation groups will be evenly and randomly spread over the three years. Unfortunately due to time constraints, this is not possible with the onion groups which will be evenly and randomly spread over only two of the years (i.e. half in each year). The two onion groups will also be able to be analysed separately, but with a reduced power of 18 subjects per group gives a power of 80% of detecting a difference in response variable of 1 standard deviation. This is quite a large effect of the enriched onions, given that they are only “equivalent” to a selenium dose of 50µg/day. This is based on a 25% drop out rate expected for the onion intervention study.

The data would be initially analysed using an ANOVA model to test for differences in end-points between the groups. If the required data assumptions for this model are not met (e.g. normality), then data transformations and/or non-parametric methods will be employed. A repeated measures analysis using all 5 data points per subject will also be used, although it is the end-point (week 12) that is of primary interest.

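### Section 7.0 lets an undefined year effect, seen in the trial's own data, decide the model and the volunteers analysed; year should be in every between-group analysis from the start, and one analysis named as the main one

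*Protocol*

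**What the plan says.** All of this is in Protocol section 7.0, with the recruitment layout in section 6.4, Table 1.

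- **Six groups, no year term.** The sample size rests on a one-way ANOVA: "our sample sizes are designed to give an 80% chance of detecting a range of plasma selenium between the six groups". The planned loss is 25%: "This allows for a drop-out rate of 25%, or in other words, finishing with 18 subjects in each group".
- **Four groups, with year.** The fallback opens "In the unlikely event of there being a year effect, and thus the two onion groups (but not the control and supplementation groups") being potentially compromised. It then drops the onion arms and uses a "two-way ANOVA model to analyse the data, with a three level year effect and a four level group effect". At 24 per group this is also given 80% power for 1 SD.
- **Onion pair.** "The two onion groups will also be able to be analysed separately", with 80% power for 1 SD at 18 per group. This sentence is not conditional on a year effect.
- **Order.** "The data would be initially analysed using an ANOVA model to test for differences in end-points between the groups". The text does not say which ANOVA. Week 12 is named as the time point of primary interest.

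Table 1 recruits 32 tablet volunteers in each of three years (8 per arm per year). It recruits 12 per onion arm in years 2 and 3 and none in year 1. The protocol states no significance level.

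**The concern.** Two separate matters are involved.

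**The switch.** The protocol does not say what counts as a year effect: which test, at what level, on which outcome. The decision changes both the model and the people in it, 144 volunteers or 4 × 24 = 96. It could differ from one outcome to the next. Until the switch operates, the analysis is a model that ignores year in a design where two of the six arms miss a whole year. A difference between years then appears as a difference between tablet and onion arms.

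**The extra test.** The onion pair is available as well as an ANOVA, and no analysis is named as the main one. If significance in either is taken as a positive finding for that outcome, the error rate is that of two tests, not one.

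At stake is whether a significant week-12 result can be read at its nominal level, and whether its basis was settled before the data were seen.

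**Working it through.** **Inputs.** Table 1 layout: 8 per tablet arm per year and 12 per onion arm in years 2 and 3 (N = 144), or 6 and 9 after 25% loss (N = 108). Section 7.0 assumes that "any effect of selenium supplementation would be proportional to the amount of supplementation", with enriched onions equivalent to 50 µg/day and un-enriched to none. With a range of 1 SD the means are 0, 0.25, 0.5, 1, 0.25, 0. Assumed: 5% level (two-sided for the pair), normal data, and year-1 shifts of 0.5 and 1 SD.

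**Step 1. The plan's own power figures.**

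- Onion pair, 18 per group, 1 SD: noncentrality 1/√(2/18) = 3 on 34 df, power 83.0%. The stated 80% is reproduced as at least 80%.
- Four groups: Σ(μ − mean)² = 1.3125 − 4 × 0.4375² = 0.547. λ = 24 × 0.547 = 13.1, power 85.8%. At 18 per group λ = 9.8, power about 73%.
- Six groups: Σ(μ − mean)² = 1.375 − 6 × 0.3333² = 0.708. λ = 24 × 0.708 = 17.0, power 89.7%. At 18 per group λ = 12.75, power 77.2%.

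An assumed 5% level is therefore broadly in line with the protocol's figures.

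**Step 2. How year enters the one-way test.** One third of each tablet arm is in year 1 and none of either onion arm. A year-1 shift of δ SD moves the four tablet means by δ/3 and leaves the onion means alone. The spurious between-group term is n × (δ/3)² × (4 × 2/6) = 4nδ²/27. With n = 24 this is 0.89 for δ = 0.5 and 3.56 for δ = 1, with no selenium effect at all.

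**Step 3. False-positive rates with no selenium effect** (simulation, 100,000 data sets per setting; first figure N = 144, second N = 108).

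| Year-1 shift | Six groups, one-way | Six groups, year in model | Four groups, year in model |
|---|---|---|---|
| 0 | 5.1% / 5.0% | 5.1% / 5.0% | 4.9% / 5.0% |
| 0.5 SD | 8.0% / 7.0% | 5.0% / 5.0% | 5.0% / 5.0% |
| 1 SD | 17.1% / 12.6% | 4.9% / 5.1% | 5.0% / 5.0% |

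**Step 4. The switch on its own.** Take the trigger to be a 5% test of year in the tablet arms, choosing only between the six-group and four-group tests. With no shift the rate is 5.1% / 5.1%; with 0.5 SD, 6.9% / 6.6%; with 1 SD, 5.2% / 5.6%. At 0.5 SD this trigger fires in only 52% / 40% of trials, so the unadjusted model is often kept when it should not be.

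**Step 5. The onion pair as an extra test, no year shift.**

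- Six-group or onion pair: 8.7% / 8.6%
- Four-group or onion pair: 9.7% / 9.7%. These use different volunteers, so 1 − 0.95² = 9.75%.
- Any of the three: 11.0% / 10.9%
- Six-group, with four-group or onion pair only after the trigger: 5.3% / 5.3%

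**Step 6. Price of always including year.** The six-group error df fall by two (138 to 136, or 102 to 100). Because the onion arms are unbalanced over years, λ falls from 17.0 to 16.55 (N = 144) and from 12.75 to 12.42 (N = 108). Power goes from 89.7% to 88.8%, and from 77.2% to 75.8%.

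**The case against.** **The protocol gives an order.** It says an ANOVA between the groups comes first, and it reserves the four-group model for a contingency it calls unlikely. That is a first analysis and a fallback, so it would be wrong to say no order exists. What is missing is the rule for moving from one to the other.

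**Choosing the test does not itself double the error.** A reader might infer that selecting on a year effect takes the rate to 9-11%. Step 4 does not support this: choosing only between the two ANOVAs stays near 5% with no year effect and at about 7% with a 0.5 SD shift. The 9-11% arises only when the onion pair counts as a further chance of success.

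**The three tests do not all overlap.** The four-group and onion-pair analyses use different volunteers and ask different questions, and section 3.0 makes the two organic forms an objective. Whether separate interventions in a multi-arm trial must share one error rate is debatable. Nothing in the document says that any one significant result will be declared the trial's answer.

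**Much of section 7.0 is sample-size justification, and an SAP may hold the rest.** The level, its division and the labelling of secondary analyses can properly sit in an SAP that is not shown; their absence is not the point here. The protocol does itself state a data-dependent choice of model and volunteers, and a main model that omits year. Those parts stand.

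**The size of any year effect is unknown.** The protocol thinks one unlikely, and the 0.5-1 SD shifts are assumptions. With no shift the one-way test is valid.

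**Conclusion.** The point holds in two limited parts.

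1. The year-effect switch has no criterion, and the model used before it operates is not protected against a difference the design cannot balance. At an assumed 5% level, the six-group one-way test has a false-positive rate of about 7-8% for a year-1 shift of 0.5 SD and 13-17% for 1 SD, against 5% with year in the model. This depends on a real year effect of that size. The year-adjusted figure also assumes that year acts alike in all groups.
2. If the onion pair is tested at 5% beside an ANOVA and either counts as success, the rate per outcome is about 9-10%, or about 11% if all three count. This depends on how results are claimed, which the protocol does not say.

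The documents do not support the stronger conclusion that the switch causes the 9-11%, or that the trial will in practice choose the most favourable of three results.

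**What to change.** In section 7.0:

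- Delete the year-effect switch. Include year as a factor in every between-group analysis, whether or not a year effect is seen. The onion arms then need not be dropped, since tablet volunteers are recruited in years 2 and 3 too.
- Compare enriched with un-enriched onions within years 2 and 3, with year in the model.
- Name one analysis as the main one for the week-12 end-point and describe the others, including the repeated-measures analysis, as supportive.

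No volunteers or samples are added. The statistical cost is two degrees of freedom in three-year analyses (one in the onion pair) and about 1 percentage point of power in the six-group test.

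Whether the onion comparison is gated behind the tablet comparison, Holm-adjusted with it, or treated as a separate question is for the sponsor to decide. A gate has a real price: the four-group test has about 73% power at 18 per group (86% at 24), so a true onion effect could go unclaimed because the tablet test missed. Holm instead requires the smaller of the two p-values to meet 2.5%. If an SAP already settles these matters, section 7.0 should be brought into line with it.

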# 4.0 Study Design

## 4.1 Overview

A 12 week intervention will be carried out in which 6 groups of 50-64y old men and women (n=24 per group) with low plasma (or serum) selenium are fed one of three doses of selenium (50, 100 or 200µg/d) as selenium enriched yeast (Se-yeast) tablet, a placebo tablet, selenium-enriched onions (equivalent to 50µg/day selenium) or un-enriched onions during the summer, autumn and winter periods (July-February). Subjects will be given an influenza viral challenge 10 weeks after starting the intervention. Volunteers will be informed that our study also vaccinates during the months December to February which is outside the traditional flu vaccination period adopted by the NHS. The precise time of vaccination for the volunteers will depend on their intervention starting date and may therefore take place in the period between December to February. Health care workers and those who are offered free flu vaccination from the NHS will not be eligible to take part in the study during the months of December to February.

The Se-yeast treatment will take place over 3 years; the onion treatment will take place during years 2 and 3 (the onions will be grown in years 1 and 2 for consumption the following year). The onions will be stored for a number of months and then incorporated into meals which will be stored at -18°C until required.

The control subjects will take a placebo and undergo the same tests. Venous blood samples will be taken pre-vaccination at baseline (week 0, 80mls), 6 (40mls) and 10 weeks (80mls) then post vaccination at 11 (80mls) and 12 weeks (80mls). Saliva samples will be obtained at baseline (pre-vaccination) and 12 weeks (post-vaccination). Blood samples will be used for the assessment of plasma selenium concentration (Q-ICPMS), plasma vitamin E (HPLC), selected selenoproteins, selenium-responsive genes, protein expression, and cellular and humoral immune response. The saliva samples will be tested for antibody titres to influenza antigens. A 24hour urine collection will be made during week 6 to determine selenium concentration.

Week 0

6

10

11

12

[figure not shown]

Up to 5 onion based test meals consumed

per week for 12 weeks

[figure not shown]

-Se

+Se

1 capsule taken every day for 12 weeks

Fasted Blood sample (60mL)

24hour urine collection

Influenza virus vaccination

Volunteer groups taking part in study

Saliva sample

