## Volunteers will be stratified by sex.

## 6.1 Supplementation Intervention with Se-yeast

Se-yeast supplementation (groups 1-4) will be studied during years 1, 2 and 3 of the project. All the pressed tablets will be identical (bar alphabetical labelling which will be carried out at manufacture) and will be labelled according to the law. Safety advice will also be given when the tablets are handed to the volunteers. One tablet will be taken each day for 12 weeks. The volunteers will also be given a record sheet where they will be asked to indicate at which times the supplement was taken each day (Annex 16).

Group 1: Se-yeast tablet (50μg Selenium/day)

Group 2: Se-yeast tablet (100μg Selenium /day)

Group 3: Se-yeast tablet (200μg Selenium /day)

Group 4: Placebo (control group).

On Day 1 of the study, the volunteer will be asked to attend the unit in the morning between the hours of 7:30 and 9:00am to give their first fasting blood and saliva sample. A scientist from the study team will be on hand to ensure that the volunteer is relaxed and comfortable. The volunteers will be asked not to brush or floss their teeth prior to arriving at the Unit as the use of toothpaste may interfere with the saliva sample to be collected. The volunteer will however be encouraged to bring their toothbrush and tooth paste with them to the unit so they may brush their teeth at an appropriate time, when all samples have been taken. All phlebotomy will be carried out by a qualified nurse at the HNU. A baseline venous sample of 80mL will be obtained for later determination of full blood count and glucose, as well as plasma (or serum) selenium levels, selected selenoenzyme activity, key selenium-responsive genes and protein levels and immune function markers**.** A saliva sample will also be collected from the volunteers after the blood has been taken, so the volunteer can stimulate their saliva glands by chewing sugar free gum while their blood is being taken. The volunteer will be asked to rinse their mouth out twice with cool water before chewing the gum and subsequently producing the saliva sample. The saliva samples will be used totest for a baseline of antibody titres to influenza antigens.

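### The initial analysis is an unadjusted week-12 ANOVA that makes no use of each volunteer's week-0 value; an ANCOVA on week 0 would add precision at almost no cost

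*Protocol*

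**What the plan says.** Section 7.0 sets the first analysis: "The data would be initially analysed using an ANOVA model to test for differences in end-points between the groups". It allows transformations or non-parametric methods if the model's assumptions fail. A further sentence reads, in part: "A repeated measures analysis using all 5 data points per subject will also be used, although it is the end-point (week 12) that is of"; its close gives that time point first importance. No covariate is named. The only additional factor is study year, in a fallback two-way ANOVA of the four tablet groups.

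The sample size rests on the same unadjusted model, a one-way ANOVA with six groups. It was chosen so that "a difference of 1 standard deviation in response variable between the minimum and maximum responding groups would be reliably detected". For plasma selenium the standard deviation used is the between-person value of 11.7.

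The baseline measurements are already in the schedule. Section 4.1 states: "Venous blood samples will be taken pre-vaccination at baseline (week 0, 80mls), 6 (40mls) and 10 weeks (80mls", followed by weeks 11 and 12. Section 6.1 lists the uses of the week-0 sample beyond the routine blood tests: "as well as plasma (or serum) selenium levels, selected selenoenzyme activity, key selenium-responsive genes and protein levels and immune function markers". Section 6.2 applies the same procedures to the onion groups. Saliva is also taken at weeks 0 and 12. Section 6.4 says volunteers are stratified by sex.

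**The concern.** When an outcome is measured before treatment and again at the end, adjusting for the first value removes the part of the between-person variation that persists. The week-12 ANOVA leaves that part in the error term.

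Chance baseline differences are not small at this sample size. With 18 per group, the standard error of a baseline difference between two groups is sqrt(2/18) = 0.33 SD, or 0.33 × 11.7 = 3.9 units of plasma selenium. With 24 per group it is sqrt(2/24) = 0.29 SD. The power calculation assumes effects proportional to dose, so a 1 SD effect at 200 µg/day implies 50/200 = 0.25 SD at 50 µg/day, for both the lowest tablet dose and the enriched onions. A typical chance imbalance is therefore larger than that assumed effect. In an unadjusted comparison, whatever share of the imbalance persists to week 12 stays in the estimate.

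At stake are the width of the confidence intervals and the power of the main comparison, in a trial with small groups and modest expected effects.

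**Working it through.** **Inputs.** From section 7.0: a range of 1 SD across six groups; 24 per group recruited; 25% drop-out, leaving 18; 80% power; one-way ANOVA. The pattern of means follows from the assumption that "any effect of selenium supplementation would be proportional to the amount of supplementation, with enriched onions being equivalent to a supplementation of 50µg/day selenium", with un-enriched onions counted as no supplementation. Two inputs are not in the protocol and are assumed here: alpha (0.05) and the week-0 to week-12 correlation r (0.2 to 0.7).

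**1. Reproduce the plan's figure.**
- Means in SD units: placebo 0, tablets 0.25, 0.5 and 1, enriched onions 0.25, un-enriched onions 0. Their average is 2/6 = 0.333.
- Sum of squared deviations: 1.375 − 6 × 0.333² = 0.7083.
- Noncentrality at 18 per group: 18 × 0.7083 = 12.75.
- Large-sample chi-square on 5 df: power 79.7%, which matches the stated 80%.
- Exact noncentral F on 5 and 102 df: power 77.2%. By this method 20 completers per group are needed for 80%.
- Drop-out: 18/0.75 = 24, as stated.
- At 24 completers per group: noncentrality 24 × 0.7083 = 17.0, exact-F power 89.7%.

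**2. Add the week-0 covariate.** Residual variance is multiplied by 1 − r², so the noncentrality is divided by it, and one error degree of freedom is lost (102 to 101). At 18 per group:

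| r | Noncentrality 12.75/(1 − r²) | Exact-F power |
|---|---|---|
| 0 | 12.75 | 77.2% |
| 0.2 | 13.28 | 79.1% |
| 0.3 | 14.01 | 81.5% |
| 0.5 | 17.00 | 89.2% |
| 0.7 | 25.00 | 97.9% |

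Power reaches 80% at r of about 0.24. At r = 0 the lost degree of freedom has no visible effect. At 24 per group and r = 0.5, noncentrality is 17.0/0.75 = 22.67 and power 96.8%, against 89.7% unadjusted.

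**3. Check by simulation, with the change score for comparison.** 4,000 runs for each r, 18 per group:

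| r | Unadjusted ANOVA | ANCOVA on week 0 | Change from week 0 |
|---|---|---|---|
| 0 | 78% | 77% | 43% |
| 0.25 | 79% | 81% | 57% |
| 0.5 | 77% | 89% | 77% |
| 0.7 | 77% | 98% | 95% |

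The change score has variance 2(1 − r) relative to the end-point, so it does worse than no adjustment whenever r is below 0.5.

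**4. What adjustment does not achieve.** For the two onion groups alone, at the 0.25 SD effect implied by the dose assumption and 18 per group, power is 11% unadjusted, 13% at r = 0.5 and 18% at r = 0.7.

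**The case against.** The strongest reply is that nothing here is an error. Under randomisation a week-12 ANOVA is unbiased, and its standard error already allows for chance baseline imbalance. The design is also internally consistent, since the model that was powered is the model named for analysis. This stands.

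A reader might infer that leaving out week 0 cost the trial its stated 80% power. The protocol does not support that. The 80% was calculated for the unadjusted model, and the gap of 2.8 points between 80% and 77.2% is the difference between a large-sample formula and the exact F. Moreover, 18 per group is the pessimistic case. Section 5.0 recruits until 144 volunteers have completed, and section 7.0 aims for the full 24 per group, where unadjusted power is 89.7%. The other two stated calculations are exceeded as well: 85.8% for the four tablet groups at 24 per group, and 83.0% for the onion pair at 1 SD and 18 per group.

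A reader might also infer that the baseline data are thrown away. They are not, because the planned repeated measures analysis includes week 0. A longitudinal model with baseline among the responses can draw on that information, although the protocol does not say how it would, and that analysis is additional to the week-12 comparison.

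The size of the gain is uncertain, and this also stands. The protocol gives no correlation. It may be low for responses that arise only after vaccination, such as antibody secreting cells. For plasma selenium, the entry limit of 95 µg/L narrows the baseline spread and tends to lower the correlation.

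Finally, covariates are often settled in a statistical analysis plan, which is not at hand. But this protocol does not leave the model open: it names an ANOVA and powers it, so the point concerns what is written.

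**Conclusion.** The point holds as a matter of efficiency. Section 7.0 names an unadjusted week-12 ANOVA as the initial analysis although a pre-treatment value of the blood markers is collected on every volunteer. The analysis is valid but less precise than the data allow.

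The benefit is conditional on the unstated correlation: about 2 points of power at 0.2, 12 points at 0.5 and 21 points at 0.7, with 18 completers per group. With 24 completers the gain is about 7 points at 0.5, from a level already near 90%. These figures assume alpha 0.05, the protocol's dose-proportional means and adjustment for baseline only. They do not show a biased analysis or a trial underpowered because baseline was omitted, and adjustment does not rescue the onion-only comparison at its implied effect. The case for the change is that the possible gain is worthwhile and the cost is negligible even if the correlation proves to be near zero.

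**What to change.** In section 7.0, state that for each outcome measured at week 0 the main week-12 model is an ANCOVA on group, with the volunteer's own week-0 value as covariate and sex included as the stratification factor. Transformations can be handled as the section already provides, applied to both the week-0 and week-12 values.

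Use week 0, not week 10: the week-10 sample precedes vaccination but follows ten weeks of intervention, so adjusting for it could remove part of the effect under study. Do not substitute a simple change from baseline, for the reason shown in the simulation. Fixing the model in advance also rules out a later choice between end-point, change and adjusted analyses.

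The cost is a sentence or two of text, no extra samples or visits, and about two error degrees of freedom (102 to 100 at 18 per group). Any further term, such as year or onion preference, would cost more and should be decided separately.
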